### Objective

2.10

#### Primary objective

2.10.1

The main objective of this study was to investigate the effects of HP versus CP in enteral nutrition on intestinal permeability in critically ill ICU patients.

#### Secondary objective

2.10.2

The secondary objective was to investigate the effects of HP versus CP in enteral nutrition on illness severity and mortality in critically ill ICU patients.

#### Intervention

2.10.3

The intervention group will receive HP enteral nutrition at a dosage of 1.6 g/kg/day, whereas the control group will receive CP enteral nutrition at a dosage of 1.2 g/kg/day. The intervention will last for 10 days in ICU-admitted patients.

#### Primary outcomes

2.10.4

•Zonulin levels will be measured to assess intestinal permeability.

#### Secondary outcomes

2.10.5

•SOFA questionnaire•30-day and 60-day mortality rates•Length of stay (LOS) in a hospital

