### Trial design

2.1

This study is a randomized, double-blind clinical trial with two groups that receive different doses of protein via enteral nutrition: the CP group and the HP group. All patients will received enteral nutrition through tube feeding. Critically ill patients admitted to the ICU will be eligible for enrollment 24 h after admission. Protein administration begins 48 to 72 h after admission, depending on the patients' suitability. The acute physiology and chronic health evaluation II (APACHE II) and modified nutritional risk in critically ill (mNUTRIC) scores will be assessed at ICU admission. Sequential Organ Failure Assessment (SOFA) score will be evaluated at the beginning and end of the intervention period. Blood samples will be collected on days 0, 5, and 10 for the measurement of zonulin levels and intestinal permeability. Serum zonulin has been widely used in clinical studies as a practical and minimally invasive biomarker reflecting intestinal barrier function [22]. Established tests for intestinal permeability, such as the lactulose/mannitol ratio, are limited in critically ill ICU patients due to practical and clinical constraints, including the need for enteral substrate administration, timed urine collection, and potential hemodynamic instability [23]. Therefore, we used serum Zonulin as a reliable biomarker for intestinal barrier function in ICU patients. [13,21,22,24]. The medication administered during the intervention will be documented and organized by drug class. During the 10-day intervention, patients will be under continuous clinical observation and full monitoring by the treatment team and will be constantly monitored for protein feeding tolerance. The blood samples will be centrifuged and frozen at −70 °C until laboratory analysis. Finally, data on zonulin levels, intestinal permeability, and clinical scores will be analyzed via SPSS and appropriate statistical methods. The trial procedure is illustrated in the flow chart presented in Fig. 2. The protocol was created following the SPIRIT guidelines (see Table 1).

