### Reasons for eliminating the data

2.6

•Expected ICU stay of less than 48 h•Patient death or discharge before day 4 of the study•Use of glutamine supplement during the study period•NPO (nil per os) status for more than 4 consecutive days•Presence of any absolute contraindication to EN•Refusal or withdrawal of consent at any stage of the intervention

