#### Statistical analysis

2.10.16

The data will be analyzed via SPSS version 25. The normality of the data will be assessed with the Kolmogorov‒Smirnov test. Descriptive statistics will include the mean ± SD for normally distributed variables and the interquartile range (IQR) for nonnormally distributed variables. Pre- and postintervention measures will be compared using a paired *t*-test, whereas frequency tables and medians will describe categorical and continuous data. Categorical variables will be analyzed via the chi-square test or Fisher's exact test, and continuous variables will be analyzed via the Mann‒Whitney *U* test. Survival analysis (Kaplan‒Meier and Cox regression) will be used for time‒to‒event outcomes, and ANCOVA will compare primary outcomes at baseline, day 5, and day 10. Potential confounders including age, sex, BMI, APACHE II score at ICU admission, admission diagnosis category, vasopressor use during the intervention, and predefined comorbidity groups will be included as covariates in multivariable regression and ANCOVA models. These adjusted analyses will be applied to both primary (zonulin levels) and secondary outcomes where appropriate to minimize residual confounding. Longitudinal regression models will assess the intervention's effect, controlling for the same confounding factors. Statistical significance will be set at p < 0.05.

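### The plan does not say how a death from study day 4 on enters hospital length of stay or the end-of-intervention SOFA; under its default tests a death ranks as a short stay and drops out of SOFA.

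*Protocol article*

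**What the plan says.** - **Outcomes.** Section 2.10.5 of the protocol article names SOFA, 30- and 60-day mortality, and "Length of stay (LOS) in a hospital". It gives no rule for a stay that ends in death.
- **SOFA schedule.** Section 2.1 states: "Sequential Organ Failure Assessment (SOFA) score will be evaluated at the beginning and end of the intervention period". Section 2.10.8 lets feeding run to ICU discharge or day 10, so the end of the intervention can be read in two ways.
- **Tests.** In section 2.10.16, "continuous variables will be analyzed via the" Mann-Whitney test, and "Pre- and postintervention measures will be compared using a paired" t-test. Kaplan-Meier and Cox methods are reserved for time-to-event outcomes, which are not named. Covariate adjustment is extended to secondary outcomes: "These adjusted analyses will be applied to both primary (zonulin levels) and secondary outcomes where appropriate to minimize residual confounding".
- **Deletion.** Section 2.6 gives as a reason for removing data: "Patient death or discharge before day 4 of the study". Nothing is said about deaths after that.

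**The concern.** In an ICU population both outcomes are cut short by death. A Mann-Whitney comparison of raw LOS places a patient who died on day 6 ahead of one discharged alive on day 20. A paired or end-score comparison of SOFA needs an end value, so a patient who died before then contributes nothing.

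LOS can therefore move opposite to mortality for mechanical reasons. If high protein raised mortality, LOS would tend to look better in that arm; if it lowered mortality, LOS would tend to look worse. SOFA is the named outcome closest to the illness-severity objective in section 2.10.2, and a survivors-only comparison can show no difference where more patients have died. The Discussion says that a zonulin reduction together with better clinical outcomes could influence feeding guidelines, so a misleading secondary result would carry weight.

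**Working it through.** The protocol has no LOS, SOFA or mortality figure to reproduce. From the documents come 44 per arm (section 2.9), the 0.05 level and the day-4 deletion (section 2.6). Everything else below is assumed.

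**LOS, by hand, before the deletion.** Assume lognormal stays that are the same in both arms: live discharge median 20 days, log-SD 0.5; death median 8 days, log-SD 0.6. Only mortality differs between the arms.

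1. Chance that a random death has a shorter stay than a random live discharge: Φ[ln(20/8) / √(0.5² + 0.6²)] = Φ(0.916 / 0.781) = Φ(1.17) = 0.88.
2. Chance that a random patient in the higher-mortality arm A has a shorter stay than one in arm B: 0.5 + (pA − pB) × (0.88 − 0.5) = 0.5 + 0.38 × (pA − pB). With equal mortality it is 0.5, as it should be.
3. Standard error of that proportion under the null: √[(44 + 44 + 1) / (12 × 44 × 44)] = √(89 / 23,232) = 0.0619.
4. Chance of p<0.05, with k = 0.38 × (pA − pB) / 0.0619: approximately Φ(k − 1.96) + Φ(−k − 1.96).

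**LOS, simulated with the deletion.** The same model was simulated with stays under 4 days removed, treating day 4 of stay as study day 4.

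| Mortality A v B | k | p<0.05, by hand, no deletion | p<0.05, simulated, with deletion | A has shorter median LOS |
|---|---|---|---|---|
| 20% v 15% | 0.31 | 6% | 6% | 59% |
| 25% v 15% | 0.61 | 9% | 9% | 68% |
| 30% v 15% | 0.92 | 15% | 13% | 74% |
| 45% v 25% | 1.23 | 23% | 20% | 84% |

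Another run of the simulation gave 5.5%, 7.4% and 12.4% for the first three rows, so the simulated column is good to within a point or two. At 30% v 15%, nearly all significant results favoured arm A (12.0 of 12.3 percentage points in one run). With equal mortality of 20% and no deletion, the rate was 5.1%, and 4.9% with deaths ranked worst.

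**LOS, a second model.** Assumptions: live-discharge median 18 days; time to death 1 day plus an exponential with mean 12 days; a severity factor linked to both death and stay; death risk 25% in one arm and 35% or 45% in the other. After the day-4 deletion, median LOS in the higher-death arm was 0.7 and 1.4 days shorter. Mann-Whitney significantly favoured that arm in 5.9% and 12.1% of trials, where 2.5% is expected. Ranking death as worst, with all 44 per arm kept, reversed the direction: significant against that arm in 6.9% and 17.2%.

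**SOFA, in the second model.** Day-10 SOFA was assumed to have mean 6 and SD 3, correlated with severity, with no true effect. Differences are higher-death arm minus the other; a positive value is worse.

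| Death risk | Survivors only | Death before day 10 scored 24, all 44 per arm kept |
|---|---|---|
| 25% v 25% | +0.04 | +0.04 |
| 35% v 25% | −0.03 | +0.96 |
| 45% v 25% | −0.05 | +1.83 |

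Among survivors the difference stays near zero, while a score that counts deaths moves by 1 to 2 points. Keeping the patients whom section 2.6 removes does not change this: survivors-only differences of +0.01, −0.05 and −0.12.

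**The case against.** The strongest reply is that the protocol never assigns LOS to the Mann-Whitney test. A reader might infer that it does, but section 2.10.16 also says that Kaplan-Meier and "Cox regression) will be used for time"-to-event outcomes, without naming them, and LOS is a duration. That stands: the method for LOS is unassigned. It does not remove the problem. Under survival methods one must still say whether death counts as a discharge, a censoring or a competing event, and the text does not.

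Second, section 2.6 already removes deaths before day 4, so it would be wrong to infer that every early death counts as a short stay. This stands too. The mechanism applies to deaths from day 4 on, and the simulated figures include the deletion.

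Third, a reader might infer that dropping the dead from SOFA favours the arm with more deaths. The calculation does not support that. The survivors-only difference is about zero; what is lost is the sight of harm.

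Fourth, handling of deaths is often left to an analysis plan, and none is shown here. Silence alone would not be a finding. Here the stated default tests and the two-point SOFA schedule, followed as written, produce the distortion.

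Finally, these are secondary outcomes, the abstract does not list LOS among them, and mortality is reported alongside, so a conflict would be visible. That limits the importance but does not remove the value of a rule fixed in advance.

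**Conclusion.** The point holds as a cheap improvement. The plan's default tests, with no rule for deaths from day 4 on, would rank an in-hospital death as a short stay and leave out of SOFA those who die before the end of the intervention.

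The direction for LOS is the same in both models. The size depends on the assumed mortality gap: almost no inflation at 5 percentage points and about four times the nominal 5% at 20 points. These sizes rest on assumed stays and death rates, since the protocol states none, and on LOS being analysed under the continuous-variable default. For SOFA the supportable statement is that harm may be hidden, not that either arm is favoured.

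The primary zonulin conclusion is unaffected. The post-randomisation deletion in section 2.6 is a separate issue and is not judged here.

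**What to change.** In section 2.10.16, before recruitment starts (the Trial registration section says that it had not begun):

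- **LOS.** Name the method. Either keep Mann-Whitney and rank in-hospital deaths as the worst outcome or, if LOS is meant as time-to-event, analyse discharge alive with death as a competing event, not as a discharge or a censoring.
- **SOFA.** State whether the end of the intervention means ICU discharge or day 10, reconciling sections 2.1 and 2.10.8. Use the score taken at that point, without adding an assessment, and rank deaths before it as the worst end SOFA.
- **Reporting.** Show survivors' LOS and SOFA descriptively beside mortality.

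The cost is a few lines of text and no new data. The downside is that a ranked outcome mixes death with duration or organ function: a difference may come from mortality alone. The components must therefore be tabulated by arm.

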#### Confounding variables

2.10.6

Potential confounding variables include age, sex, BMI, APACHE II score at ICU admission, admission diagnosis category, vasopressor use during the intervention, and underlying comorbidities. Comorbidities will be categorized into predefined clinical groups, including Trauma, cancer, surgery, diabetes mellitus, kidney disease, cardiovascular disease, and liver disease. These factors should be measured and considered, as they may influence outcomes.

#### Protein in enteral

2.10.7

The amount of protein administered is based on the patient's body weight. A portion of the protein requirement is met through conventional enteral nutrition formulas, while the remaining portion is supplemented with whey protein. To prevent an increase in osmolarity and enhance patient tolerance, less than 10 g of protein are administered in divided doses throughout the day.

#### Enteral protein administration

2.10.8

Gavages will be administered by personnel blinded to the baseline assessments. Once each patient's hemodynamic status is stabilized, tube feeding (via a nasogastric tube or gastrostomy) is initiated. High-protein feeding begins 48 h after ICU admission and continues until either ICU discharge or day 10 of the study. Enteral feeding will be given intermittently every 3 h. The feeding volume will be determined on the basis of each patient's caloric requirements and tolerance. During the first 24 h, 30% of the total caloric need will be initiated. If well tolerated, the volume was gradually increased to the target level. The protein and energy goals should be increased gradually and achieved within the first 48 to 72 h to avoid overfeeding.

#### Energy requirements

2.10.9

Sufficient energy is necessary to maintain vital functions, prevent muscle catabolism, and support patient recovery. Energy restriction during the initial days is necessary to reduce the risk of refeeding syndrome. We should carefully monitor energy intake, especially in patients at risk of malnutrition. For mechanically ventilated patients, excessive energy intake may lead to increased CO_2_ production, impaired ventilation, and prolonged dependence on the ventilator. In addition to energy, adequate attention must be given to protein requirements, which are critical for preserving lean body mass, as well as fluid and electrolyte balance. During the first 3 to 5 days of hospitalization, energy intake should begin at 15–20 kcal kg/day. Once hemodynamic stability is achieved, intake should be gradually increased to 25–30 kcal/kg/day [19]. Additionally, energy requirements should be adjusted on the basis of individuals’ BMI, as illustrated in the table below.

**Table undtbl1:** 

BMI (kg/m^2^)		Body weight	
<18.5			Initial: 15–20 kcal/kg Target: 25–30 kcal/kg
18.5- 29.9		Actual Body Weight	25-30 kcal/kg
>30	30-50	Actual Body Weight	11-14 kcal/kg
	>50	Adjusted Body Weight	22-25 kcal/kg

#### Demographic questionnaire

2.10.10

A demographic questionnaire will also be completed, including age, sex, ethnicity, education level, marital status, occupation, smoking status, special diets, comorbidities, medications, and the use of dietary supplements. Trained personnel will take anthropometric measurements, including weight, height (or ulna length), and arm circumference.

#### Zonulin

2.10.11

Zonulin levels will be measured in blood samples. Blood samples (5 ml) will be taken from patients before the intervention and again on days 5 and 10 to measure zonulin levels. After centrifugation, the serum will be separated. Zonulin levels in the serum sample will be measured via a sandwich ELISA. The method involves incubating a sample with a specific antibody against zonulin, followed by subsequent detection of the bound zonulin using a secondary antibody and a colorimetric substrate.

#### Apache II score

2.10.12

The APACHE II score is used to classify patients according to disease severity and assess their baseline health status before admission to the ICU and includes the acute physiology score (which is based on 12 physiological variables), age adjustment, and chronic health evaluation. The total score ranges from 0 to 71. Higher scores can be associated with greater disease severity and risk of mortality.

#### SOFA score

2.10.13

The SOFA score assesses six major organ systems**,** such as cardiovascular, nervous, respiratory, coagulation, renal, and hepatic systems. In each system, a score of 0 indicates normal functioning, a score of 4 indicates organ dysfunction, and the total score ranges from 0 to 24. Higher SOFA scores are associated with a poorer prognosis, indicating greater degrees of organ dysfunction, poorer clinical outcomes, and increased mortality risk**.**

#### mNUTRIC score

2.10.14

The NUTRIC questionnaire is the first nutritional risk assessment tool specifically validated for patients in the ICU. This study used a modified version of the NUTRIC score (excluding interleukin-6). The mNUTRIC score ranges from 0 to 9 and is calculated on the basis of clinical data collected during the first 24 h after ICU admission. Scores of 4 or higher indicate high nutritional risk, whereas scores below 4 indicate low nutritional risk.

#### Mortality

2.10.15

Mortality will be followed up on days 30 and 60 postintervention, with the use of the hospital information system (HIS) by entering the patient's national ID or through phone contact.

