**Methods:**

Participants were selected from 88 adult patients with critical illness aged 18-65 years who were admitted to the ICU of Hazrat Rasoul Akram Hospital in Tehran. In this randomized controlled clinical trial, patients will be allocated randomly into two groups of 44. The intervention group will receive high-protein (HP) enteral nutrition (1.6 g/kg/day), and the control group will receive conventional-protein (CP) enteral nutrition (1.2 g/kg/day) for 10 days. The primary outcome will be the change in serum Zonulin levels during the intervention period. Zonulin will be measured on days 0, 5, and 10. The SOFA, APACHE II, and mNUTRIC scores will also be assessed. Mortality will be calculated at 30 and 60 days after the intervention. The secondary outcomes will be SOFA score and 30- and 60-day mortality.

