### Sample size

2.9

The sample size was determined on the basis of serum zonulin levels, which were considered the primary outcome of the study. In the study by Klaus et al. [21], the mean zonulin level in the target patient population was reported to be 3.40 ng/mL, with a standard deviation of 0.71. A type I error (α) of 0.05 and a statistical power (1−β) of 80% were used for the calculation. A 10% change in zonulin levels was deemed clinically significant. This threshold was chosen based on previous reports of variation in zonulin levels in critical illness and feasibility considerations for sample size estimation [21]. The exploratory nature of this outcome is acknowledged. Using the standard formula for sample size estimation based on a two-sided independent samples *t*-test to determine the mean of the intervention group versus the control group, the required sample size was calculated to be 41 participants per group, or a total of 82 participants. The final sample size was adjusted to 44 participants in each group, out of a total of 88 participants, considering an expected attrition rate of 5% during the study period.

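### The 30- and 60-day mortality time points are set after the intervention instead of from randomisation, so the window may vary by patient and deaths during feeding have no defined place

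*Protocol article*

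**What the plan says.** All references are to the protocol article.

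- **Time point.** Section 2.10.15 (Mortality): "Mortality will be followed up on days 30 and 60 postintervention". Abstract, Methods: "Mortality will be calculated at 30 and 60 days after the intervention".
- **Outcome list.** Section 2.10.5 gives only "30-day and 60-day mortality rates", with no starting point.
- **End of the intervention.** Section 2.10.8 says that feeding "continues until either ICU discharge or day 10 of the study". Section 2.10.3 says: "The intervention will last for 10 days in ICU-admitted patients". The abstract also gives 10 days.
- **Data removed.** One reason for elimination in section 2.6 is "Patient death or discharge before day 4 of the study".
- **Analysis.** Section 2.10.16: "Survival analysis (Kaplan‒Meier and Cox regression) will be used for time‒to‒event outcomes". It states no time origin.

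No section counts mortality from randomisation or enrolment. No section says whether a death between day 4 and the end of feeding enters the 30- and 60-day rates.

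**The concern.** In a randomised comparison of mortality, the clock should start at a moment that treatment cannot influence. Randomisation is such a moment; the end of the intervention is not. Three consequences could follow.

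1. If feeding ends at ICU discharge, the date that starts the 30 or 60 days differs between patients. Time to ICU discharge may itself respond to the feeding regimen, so the two arms could be observed for different lengths of time.
2. A patient who dies on study day 6 dies before any postintervention period begins. If survival is timed from the end of feeding, that death has a survival time of zero (feeding ends at death) or a negative one (feeding nominally ends on day 10).
3. Deaths before day 4 are at risk of being lost altogether through section 2.6.

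The feeding period is when the arms actually differ in protein intake, so deaths in that period bear directly on the secondary objective in 2.10.2. Section 3 (Discussion) says that improved clinical outcomes could influence guidelines on protein dosing.

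**Working it through.** The article gives no mortality rate, event count or power for mortality, so there is no figure of the plan to reproduce. The sample size in 2.9 rests on zonulin alone and does not bear on this point. Every death rate below is an assumption.

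**Step 1. Length of the window.** Inputs: feeding ends at ICU discharge or day 10 (2.10.8), and patients who leave before day 4 are eliminated (2.6, reading discharge there as ICU discharge). For a retained patient whose feeding ends on study day E, the time points fall on E + 30 and E + 60.

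| Feeding ends on day | '30-day' falls on day | '60-day' falls on day |
|---|---|---|
| 4 | 34 | 64 |
| 7 | 37 | 67 |
| 10 | 40 | 70 |

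The spread is 6 days. Under the fixed 10 days of 2.10.3 and the abstract, only the last row applies and the window does not vary.

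**Step 2. All deaths counted, only the window differs.** Assume a constant hazard with 30% dead at day 30. Mortality by day T is then 1 − 0.70^(T/30). Suppose feeding ends on day 10 on average in one arm and earlier in the other.

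| Mean end of feeding | T | Mortality | Difference from day 10 |
|---|---|---|---|
| Day 10 | 40 | 37.85% | – |
| Day 8 | 38 | 36.35% | 1.50 points |
| Day 6 | 36 | 34.82% | 3.03 points |
| Day 4 | 34 | 33.25% | 4.60 points |

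The hazard is the same in both arms, so these 1.5 to 4.6 points come from the window alone.

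**Step 3. Deaths during feeding left out.** Let p1 be the risk of death during feeding and p2 the risk in the next 30 days among survivors. The full risk is p1 + (1 − p1) × p2. A count of survivors from the end of feeding sees only p2. CP is the control arm and HP the intervention arm; differences are HP minus CP.

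| Assumed p1, CP / HP | Assumed p2, CP / HP | Difference, survivors only | Difference, all deaths |
|---|---|---|---|
| 15% / 15% | 15% / 15% | 0.0 | 27.75% − 27.75% = 0.0 |
| 20% / 10% | 15% / 15% | 0.0 | 23.5% − 32.0% = −8.5 points |
| 10% / 20% | 15% / 15% | 0.0 | 32.0% − 23.5% = +8.5 points |
| 25% / 10% | 15% / 20% | +5.0 points | 28.0% − 36.25% = −8.25 points |

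For the second row: CP 0.20 + 0.80 × 0.15 = 0.320; HP 0.10 + 0.90 × 0.15 = 0.235.

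With equal risks in both arms (first row) there is no distortion. With unequal early deaths, a real difference in either direction can vanish, or a benefit can appear as harm.

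**The case against.** The strongest reply is that both mortality sentences may only say when vital status is checked, through the hospital system or by phone. A cumulative count at those checks would include a death on day 6. If the intervention is taken as the planned 10 days, the checks fall on about day 40 and day 70 for everyone, with no variation and no influence of treatment. The missing origin for Kaplan–Meier and Cox is a detail that an analysis plan may supply.

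Much of this stands. A reader might infer that deaths during feeding are excluded, that the survival analyses are timed from the end of feeding, or that the arms will certainly not be comparable. The article supports none of these. It does not say that deaths from day 4 onward are dropped, it states no survival origin, and Step 3 shows no distortion when risks are equal. The varying window rests on 2.10.8, which conflicts with 2.10.3 and the abstract.

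The reply does not remove the point. The only clock that the article states starts after the intervention, so this is a stated choice and more than an omitted detail. With a fixed day-10 start, deaths on days 0 to 10 still precede that start, and whether they count is left to the reader. A cumulative count would still be affected by the elimination in 2.6 and, under 2.10.8, by unequal windows.

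**Conclusion.** The point holds as a conditional risk. The mortality time points are tied to an event after randomisation. Under 2.10.8 that event varies by patient and may be affected by treatment, which gives windows of about study day 34 to 40 and 64 to 70. Deaths during feeding have no defined place, and data on those before day 4 are set to be eliminated.

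Bias arises only if early deaths or feeding duration differ by arm. The likely size cannot be derived from the article. On the assumed rates it is 1.5 to 4.6 points when all deaths count and mean feeding ends 2 to 6 days earlier in one arm. It can exceed 8 points when deaths during feeding are left out and their risk differs by 10 to 15 points between arms. Mortality is secondary and the primary zonulin comparison is untouched, so this should be fixed but is not critical to the trial.

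**What to change.** 1. In the abstract and 2.10.15, define 30- and 60-day mortality as death from any cause from randomisation to fixed days 30 and 60, in all randomised patients, counting deaths during feeding and before day 4.
2. In 2.10.16, state randomisation as the time origin for Kaplan–Meier and Cox, with censoring at day 60 or at last known contact.
3. In 2.6, exempt mortality from the elimination rules, so that vital status is kept for every randomised patient as far as consent to follow-up allows.
4. State how study day 0 relates to randomisation. Section 2.1 allows enrolment from 24 h after ICU admission and starts protein at 48 to 72 h, so the two may not coincide.
5. Reconcile 2.10.8 with 2.10.3 and the abstract on when the intervention ends. With the clock at randomisation, the mortality endpoint no longer depends on the answer.

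The cost is small. No extra patients, visits or data sources are needed, follow-up ends slightly earlier, and the hospital system and phone contact serve as before. The article says that recruitment has not begun, so the change can be made before any patient is affected.
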